#### Statistical Analysis

The data analysis will be descriptive, using frequency and percent for categorical measures and mean (SD and range) for quantitative outcomes. No a priori hypotheses will be tested. The 80% CIs will be computed to describe the precision of the estimates for both aims and to guide sample size determination for the larger study.

The qualitative analysis will be based on data from a focus group comprised of caregivers of child participants involved in the study and interviews as needed for those who cannot attend the focus group. The interviews will be conducted and recorded in Spanish, transcribed, and translated into English and checked for accuracy. Coding will be completed by two researchers, first individually and then they will meet to discuss and agree upon codes. Researchers will utilize an inductive process to thematically analyze codes.

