**Objective:**

This protocol describes the rationale, design, and methods of the “Thirsty for a Smile” feasibility study. The aim of the study is to assess the feasibility, acceptability, and appropriateness of a dietary intervention promoting water consumption in lieu of sugar-sweetened beverages among young patients, mostly from Latino heritage.

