A comprehensive approach that targets the main causes of the disease is necessary to improve the clinical outcomes for severe dental caries [26]. Unfortunately, the trials of one-on-one dietary counseling undertaken in dental settings have been neither promising nor rigorous [27]. Dietary management of other chronic diseases—specifically childhood obesity—has been successfully implemented in studies [28-30] and can be adapted to clinical settings. Evidence is mounting that interventions to reduce the consumption of SSBs [28,29,31-36], including interventions promoting water consumption to displace SSBs [30], can be effective. Many children with severe ECC (S-ECC) are treated in major academic health centers or hospitals with programs in pediatric dentistry. These centers have sufficient scale to implement new, more effective approaches to the secondary prevention of ECC. Moreover, the lessons learned from preventing recurrent disease can also be applied to primary prevention. Reducing the consumption of SSBs and promoting the consumption of water is an appropriate strategy to prevent dental caries and other chronic diseases.

The primary objective of the proposed study is to test the feasibility of an environmental dietary intervention designed to promote the consumption of water, in lieu of SSBs, on dental caries relapse among Latino and non-Latino children. A secondary objective is to investigate the acceptability of the environmental dietary intervention strategies and tools among families and patients. This short-term feasibility project will refine the study methods and data collection tools to effectively plan and perform a randomized controlled trial (RCT).

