### Ethics and Confidentiality

The Institutional Review Board (IRB) of the University of Washington (UW) will serve as the IRB of oversight for this study. The protocol, informed consent form(s), recruitment materials, and all subject materials will be submitted to the IRB for review and approval. Approval of both the protocol and the consent form must be obtained before any subject is enrolled. Any amendment to the protocol will require review and approval by the IRB before the changes are implemented in the study.

A consent form describing the detailed study procedures and risks will be given to the potential participant. The investigator or designee will explain the research study to the potential participant and answer any questions that may arise. Study staff conducting the consent process will be bilingual (English and Spanish) to accommodate non-English speakers. All study forms and materials will be available in Spanish and English. Participants will elect their preferred language for all communications. The consent process will be documented in the clinical or research record.

Study participant confidentiality is strictly held in trust by the investigators, study staff, and the sponsor(s) and their agents. This confidentiality is extended to cover any study information relating to subjects. The investigator will ensure that this study is conducted in full conformity with the principles set forth in The Belmont Report: Ethical Principles and Guidelines for the Protection of Human Subjects of Research, as drafted by the US National Commission for the Protection of Human Subjects of Biomedical and Behavioral Research (April 18, 1979) and codified in the US Code of Federal Regulations Title 45: Public Welfare, part 46 and/or the International Council for Harmonisation’s Guidelines for Good Clinical Practice E6.

This project does not meet the National Institutes of Health (NIH) definition of a clinical trial as it will not study the cause-and-effect relationship between an intervention and a health outcome. Therefore, this study will not be registered in a public trials registry such as ClinicalTrials.gov.

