### Participants and Setting

Inclusion criteria for parents/caregivers and child dyads for enrollment include providing a signed and dated consent form, willingness to comply with all study procedures, availability for the duration of the study, a child aged 2 to less than 9 years, a diagnosis of S-ECC, previous treatment for ECC under general anesthesia, and a child in good general health based on parent self-report. The study clinical site treats approximately 700 pediatric patients with ECC per year; approximately 500 of these patients would be eligible to participate in the study with a goal of enrolling 21 participants. Exclusion criteria for parents/caregivers and child dyads include a parent/caregiver under 18 years of age or a child with American Society of Anesthesiologists Physical Status IV or higher.

Caregivers will be recruited by the onsite research coordinator during the initial examination visit at the dental clinical site once the child is determined to have S-ECC and to meet the other eligibility requirements. A promotional pamphlet or flyer will be distributed to caregivers of children scheduled to undergo surgical treatment for S-ECC by the research coordinator.

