#### Secondary Objectives

We will assess the acceptability, appropriateness, and perceived feasibility for each of the intervention components and health assessments, and the willingness to participate in a longer trial (1-year intervention plus 1 additional year of follow-up) (≥80%).

The questions to assess the intervention components were developed by the investigators and participants will be asked to rate each component on a scale from 1 to 10. Acceptability of survey completion will be assessed using questions adapted from Wolpin et al [57], which have been used to assess acceptability of an electronic self-report program for cancer patients. The six Likert-scale items, measured from 1 (“not at all”) to 5 (“very much”), ask about ease of use, satisfaction, helpfulness, and completion time.

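### The qualitative interviews are set in Spanish although participants choose their language for all communications, so English-preferring caregivers may be missing or under-represented in the qualitative data

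*Protocol article*

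**What the plan says.** The Statistical Analysis section bases the qualitative analysis on one focus group of caregivers, supplemented by "interviews as needed for those who cannot attend the focus group". The next sentence fixes the language: "The interviews will be conducted and recorded in Spanish, transcribed, and translated into English and checked for accuracy". It gives no English alternative and no reason for the restriction, and it does not state the language of the focus group separately.

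The Ethics and Confidentiality section sets the general rule: "Participants will elect their preferred language for all communications". It adds: "All study forms and materials will be available in Spanish and English". Staff who conduct the consent process are to be bilingual.

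On the population, the objective in the Introduction is worded "on dental caries relapse among Latino and non-Latino children", and the abstract describes the intervention as being tested "among young patients, mostly from Latino heritage". Participants and Setting lists no language or ethnicity criterion. Its two exclusions are a caregiver under 18 and a child with anesthesia risk status IV or higher.

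On acceptability, Secondary Objectives uses ratings. For the intervention components, "participants will be asked to rate each component on a scale from 1 to 10". Acceptability of survey completion is measured by six Likert items scored 1 to 5.

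**The concern.** A research interview with a caregiver is a communication with a participant. The ethics section promises a choice of language for all of these, and the analysis section removes that choice for one of them. A caregiver who elects English would either be interviewed in a second language or not contribute to the qualitative strand.

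This strand matters because the Design section calls the study mixed methods, and the focus group and interviews are its only qualitative source. Ratings show how well a component was liked. Open answers are where caregivers can say why, and the Conclusions promise an intervention suited to the people who will use it as the basis for a randomized trial. If language decides who is heard, the themes may be read as those of all enrolled families when they come from one part of them. The Limitations section concedes that results may be specific to the community and setting, but it does not mention a language restriction.

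**Working it through.** The article states no figure on this point, so there is none to reproduce. The check is a comparison of sections, followed by one illustrative calculation.

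**1. Do the two rules conflict?** The ethics section covers all communications and makes no exception. The analysis section names Spanish and attaches no condition such as the caregiver's preference. For a caregiver who elects Spanish the two agree. For one who elects English they do not.

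**2. Can a caregiver who elects English be enrolled?** Yes. The exclusion sentence begins "Exclusion criteria for parents/caregivers and child dyads include a parent/caregiver under 18 years of age" and adds only the child's anesthesia status. No inclusion criterion concerns language. The objective names non-Latino children, and the abstract says mostly, not only, Latino. Providing all forms in English also shows that such caregivers were foreseen.

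**3. Which results are exposed?**

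| Result | How it is obtained | Open to an English-preferring caregiver? |
|---|---|---|
| Component ratings, 1 to 10 | Study questions | Yes, forms are in both languages |
| Acceptability of survey completion, six items, 1 to 5 | Study questions | Yes |
| Willingness to join a longer trial (target ≥80%) | Asked of participants | Yes, under the language-choice rule |
| Focus group | Language not stated separately | Unclear |
| Individual interviews | Spanish | Not in English, as written |

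Only the last two rows are at risk.

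**4. Does the reading of the interview sentence matter?** If it covers the focus group as well, an English-preferring caregiver has no route in their own language. If it covers only the make-up interviews, the focus group has no stated language, and an English-preferring caregiver who cannot attend it is still offered Spanish. The sentence needs correcting on either reading.

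**5. Would the conflict arise in practice?** The share q of caregivers who prefer English is not in the documents. The values below are assumptions, and caregivers are treated as independent. With n = 21 (Power section), the probability that at least one enrolled caregiver prefers English is 1 − (1 − q)^21:

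- q = 0%: 1 − 1^21 = 0
- q = 5%: 1 − 0.95^21 = 0.66
- q = 10%: 1 − 0.90^21 = 0.89
- q = 20%: 1 − 0.80^21 = 0.99
- q = 30%: 1 − 0.70^21 = 0.999

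Even a small share would probably bring the conflict into play. The calculation says nothing about how many caregivers would then be missing from the qualitative data.

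**The case against.** The strongest reply is that the Spanish sentence only describes how Spanish recordings are processed, and that the general rule still governs anyone who elects English. A journal article is also a condensed account, and an interview guide that is not shown may settle the matter. This has some force, because no section expressly excludes an English-preferring caregiver from the focus group or the interviews, and someone who prefers English may also speak Spanish. So exclusion is a risk and not a certainty. It does not remove the contradiction, because the article is not silent here. It states a language without condition, and its own ethics section says otherwise.

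A reader might infer more than the documents support:

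- **That these caregivers drop out of the acceptability results.** They do not. Acceptability, appropriateness and perceived feasibility are measured by ratings that the ethics section makes available in English. The article does not tie the focus group to any named secondary outcome.
- **That a count of lost dyads can be given by multiplying 21 by an assumed share.** This also needs all 21 caregivers to give qualitative data otherwise, and none of the English-preferring ones to take part in Spanish. The article plans one focus group with interviews as needed and sets no coverage target. Ethnicity is not language, so the wording of the objective gives no share either.
- **That views on bottled water differ by language group.** The Discussion says only that many potential families who have immigrated distrust tap water. It makes no comparison between groups.

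**Conclusion.** The contradiction stands, and its consequence is limited. Following the analysis section as written can exclude or under-represent English-preferring caregivers in the focus-group and interview data of a study that is open to them. Their number is unknown and may be zero.

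The effect is confined to the qualitative strand. The primary feasibility targets, the sample size of 21, the 80% confidence intervals and the rated secondary outcomes do not depend on it. The conclusion assumes that the interview sentence means what it says and that no document outside the article provides an English route. This is a minor correction, worth making because it is cheap and because the randomized trial may inherit the wording.

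**What to change.** Amend the Statistical Analysis section so that the focus group and/or interviews are held in the language the caregiver has elected. Caregivers who prefer English can be offered the individual interview already planned for those who cannot attend the group. Translate only where needed, and have the same two researchers code all transcripts by the same procedure.

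Report how many caregivers contributed in each language. If only Spanish speakers contributed, say so and limit the qualitative conclusions to them. Separate themes by language are not called for, since they could rest on a handful of people.

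The Results section says the study ran from March to November 2019 and that analysis is under way. For this study the remaining remedy is therefore the reporting, and the corrected wording belongs in the protocol of the randomized trial.

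The cost is a small amount of extra interview scheduling. English interviews would need no translation. Bilingual staff are stated only for the consent process, so someone able to interview in English would have to be confirmed.

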## Results

Funding has been obtained from the National Institute of Dental and Craniofacial Research (NIDCR) and the UW IRB has approved the study. The feasibility study was conducted from March until November 2019. Data analysis is currently underway and the results are expected to be published by the end of 2022.

## Discussion

### Hypothesis and Significance

We hypothesize that a combined dietary environmental and counseling intervention—home delivery of bottled water and parental counseling regarding water consumption—will lengthen the time to onset of new dental caries relative to the current standard of care for pediatric patients with S-ECC. The intervention to be evaluated in this study is family-focused [58] and introduces new familial norms by making changes in the home environment (more attractive water choices, fewer SSBs, and parental role-modeling of a preference for water over SSBs). It is expected to strengthen caregiver self-efficacy for implementing change in the child’s diet. Parents assume a leadership role in implementing the intervention and in negotiating buy-in from other adults and older children present in the home.

The main behavioral change techniques used will be physical environmental restructuring by adding an object to the environment (water bottles with fluoridated water delivered twice a month to the home environment for 2 months). Water bottles are being used because they are acceptable to the families and because many of the potential participating families—who have immigrated to the United States—distrust tap water safety [59-61].

The physical environmental restructuring will be supported by providing a service (behavioral counseling) to restructure the social environment of the child using self-regulatory techniques. Behavioral counseling to caregivers about healthy drinking for their children will change parental skills and self-efficacy on the child’s healthy drinking. Consumer Information Processing Theory [62] posits that health information must be wanted, understood, and presented at a time the patient is most receptive. Thus, we will initiate the behavioral counseling at the child’s first recall visit to the dental clinic following surgery, typically 14-21 days postdischarge, when parents and children are no longer preoccupied by the upcoming surgery but are in an early stage in their transition to reestablish home routines.

The in-person and telephone check-in sessions consist of motivational techniques [63] to increase the parents’ self-efficacy [64] about their ability to increase their child’s water drinking and decrease their SSB consumption. These sessions include volitional techniques to facilitate realistic goal-setting [65] and to translate intentions into routine practices (eg, action and plans) [66]. Throughout, parents are encouraged in “cope planning,” to identify factors that support or hamper behavior change, and make plans to bring about the supportive factors and overcome the barriers [66]. The final in-person session focuses on plans to maintain behavior changes in the absence of the home water delivery and a discussion of relapse prevention.

### Limitations

The sample size is relatively small and the length of time for the intervention is only 2 months. As noted, this is a feasibility study and larger studies will be needed to provide adequate power and assess the effectiveness of the intervention in decreasing S-ECC. Participation may be hindered by the nature of human behavior and the time constraints of families with multiple children with competing needs. Because our focus here is on ECC, we have a limited age range; however, children older than 8 years may also benefit from this dietary-environmental intervention. The feasibility and acceptance outcomes may not be generalizable and may be specific to the community and setting. However, the feasibility study will allow the investigators and the clinical site staff to test recruitment and retainment of participants, intervention delivery, and outcome assessments at the clinical site.

### Conclusions

Expected outcomes of this study will provide a basis for a successful RCT. Results of this project will produce an intervention suited to the environment and people who will use it, and will indicate challenges and opportunities for refinement of the intervention and study procedures, including how much and what type of support are needed, and how much staff time and resources it will take to implement the study.

## Appendix

Multimedia Appendix 1 National Institute of Dental and Craniofacial Research (NIDCR) Peer Review Report.

## Abbreviations

ECC: early childhood caries
GCP: Good Clinical Practice
IRB: Institutional Review Board
NIDCR: National Institute of Dental and Craniofacial Research
NIH: National Institutes of Health
OHRP: Office for Human Research Protections
RCT: randomized controlled trial
REDCap: Research Electronic Data Capture
S-ECC: severe early childhood caries
SES: socioeconomic status
SSB: sugar-sweetened beverage
UW: University of Washington
